## Abstract

**Introduction:**

The need for an interdisciplinary multimodal approach to the treatment of back pain has already been demonstrated by various studies. However, when considering the periods of incapacity to work in the longitudinal course after the multimodal pain therapy (MPT), limits in terms of its sustainable effect become clear. Patients who receive MPT subsequently return to standard outpatient care, which is associated with a risk of relapse. A 12-month relapse prophylaxis (RP) programme, intended to follow a 4-week MPT, was developed to help patients make the transition to health-conscious and physically active behaviour in everyday life and to identify and prevent impending relapses at an early stage. The evaluation, based on a cluster randomised controlled trial, seeks to provide information on the benefits of early and intensive RP as part of MPT, examine whether it is cost effective, reduces the days of incapacity to work and increases functional capacity, as well as to examine other parameters.

**Methods and analysis:**

The study population comprises members of a regional statutory health insurance fund in Germany, who are ≤62 years old, gainfully employed and have been incapacitated for work for at least 21 days due to a diagnosis of back pain. Over a recruitment period of 24 months, a maximum of 368 individuals can potentially be included in the MPT. The intervention group (IG) and control group (CG) will both receive MPT, after randomisation IG will receive RP and CG will receive no further therapy or support as part of the trial. The evaluation is carried out on the following levels: structural, process and results quality. Cost effectiveness is also assessed by means of a health economic evaluation. In addition to the collection of qualitative and quantitative primary data, claims data from the regional health insurance fund are also included in the analysis.

**Ethics and dissemination:**

This study has received approval by the ethics committee of the Hannover Medical School (reference number: 8548_BO_S_2019). The study results will be disseminated in national and international journals and conference presentations.

**Trial registration number:**

DRKS00017654.

STRENGTHS AND LIMITATIONS OF THIS STUDYA comprehensive evaluation will be provided regarding the ability of this new treatment approach in form of relapse prevention to treat back pain adequately and, furthermore, support patients in their behaviour and motivation to take care of their back health themselves before chronicity occurs.The results will contribute a better understanding of whether the acceptance of the programme could be increased by involving and closely accompanying the patients and providing them with concrete training instructions, which highlights high demands on the treatment concept that are not covered by standard outpatient care.The primary outcome is not collected via questionnaires but rather via claims data, so that an information bias can be excluded in this respect.As a cluster-randomised study with monthly randomisation, a certain degree of contamination, due to personnel changes, for example, is unavoidable, which is a limitation of the methodology.As a limitation for the primary outcome, it should be taken into account that the days of incapacity to work are based on incapacity certificates issued by the treating physician, which are usually only submitted to the health insurance funds for incapacity to work lasting 3 days or longer, but since a period of incapacity to work for more than 2 days is usually to be expected in the case of back pain, the impact is likely to be small.

## Introduction

Back pain has a high prevalence in today’s society and is one of the most common complaints in the population. In addition to frequency of occurrence, the main criteria for the assessment of back pain are severity, extent of functional impairment and prognosis with regards to return to functional and thus work capacity. Data on the prevalence of back pain in Germany include results from several regional and national surveys. The range of the prevalence lies between 30% and 70%, depending on the period considered (point prevalence, 7-day, 3-month and 1-year prevalence).^1^ The lifetime prevalence for back pain in Germany ranges from 74% to 85%.^2^ In terms of chronic back pain, the lifetime prevalence lies between 24% and 30%.^3^ With regards to incapacity to work, there are various references in the literature.^2 4–6^ Sixty eight per cent to 86% of patients with acute low back pain return to work within 1 month.^4^ The recurrence rate of low back and neck pain is 47%–63%, the relapse rate into inability to work is 33%.^1 5 7^ Relapse refers to the recurrence of back pain after temporary improvement. Musculoskeletal disorders are among the most expensive diseases in industrialised countries.^8^ According to the 2008 Federal Health Report, the costs of non-specific low back pain amounted to €3.6 billion.^2 8^ The majority of these costs are due to chronic low back pain and indirect costs resulting from the loss of patients’ ability to work. Wenig *et al* estimated the average total costs of back pain per patient to be €1322 per year.^9 10^ As a cause of premature retirement due to reduced earning capacity, musculoskeletal disorders have taken second place in recent years after mental illness and behavioural disorders.^2 8^ A large percentage of the elderly population suffers from one or more musculoskeletal disorders. However, chronic back pain, reported by about a quarter of women and 17% of men in Germany, often affects younger people in working life.^11^

Back pain is usually treated in a monodisciplinary manner, although psychosocial risk factors in particular often hinder recovery and require a multimodal approach with close content-related therapy consultation.^12 13^ Interdisciplinary multimodal treatment is not yet implemented in standard outpatient care.

Interdisciplinary multimodal pain therapy (MPT) describes the simultaneous, comprehensive treatment in which various somatic, physical and psychological interventions are integrated according to a predefined treatment plan with an identified therapeutic goal. The treatment is provided in small groups with a maximum of eight patients by a team of therapists consisting of physicians, psychologists or psychotherapists and other disciplines such as physiotherapists and others.^14^ MPT is currently considered the gold standard in pain management and treatment for patients with chronic or potentially chronic back pain.^15^ The efficacy of interdisciplinary MPT in the treatment of chronic or recurrent back pain with risk of chronification has already been proven in various studies.^8 13 14 16–20^ The term recurrent describes pain episodes that reoccur after a symptom-free period of at least 6 months.^8^ Chronification, moreover, describes the transition from temporary to permanent, or chronic, back pain. After successful MPT, patients usually return to the monodisciplinary treatment of their general practitioner or orthopaedist. As a result, the risk of recurrence remains with the end of MPT. The goal of this new approach to the treatment of back pain is to achieve sustainability of MPT by combining MPT with relapse prophylaxis (RP). Thus, what is learnt during multimodal treatment in terms of physical activity and lifestyle can be applied to everyday life in the long term.

The intervention examined in this study, the 12-month RP programme, immediately follows the 4-week MPT. Like the MPT, the RP will be performed by the Rehabilitation Center, Bad Zwischenahn, on an outpatient basis. The rehabilitation centre is completely independent of the evaluating institution. The RP aims not only to provide prophylaxis against chronifying back pain relapses but also to support life-integrated physical activity. RP is the all-important link between the curative MPT phase beforehand and the patient’s physical activity afterwards. The patient will be assigned to one of three RP paths at the end of the MPT as part of an assessment during the interdisciplinary rounds and team meetings. The paths correspond to RP programmes with three different intensities (low, medium and high) for which the patient will be selected based on the severity of his or her complaints (see figure 1).

**Figure 1 F1:**
[figure not shown]
Treatment algorithm.

The low intensity level will include the opportunity for telephone consultation and the maintaining of an exercise diary as well as an obligatory telephone conversation after 6 weeks. After 6 months and again after 1 year, a 3-hour training session will take place at the Rehabilitation Center with performance tests, examination of the exercise diary and therapeutically supervised training by physiotherapists and orthopaedists. In addition, a psychological group session will be conducted by psychologists.

The medium intensity level will additionally include a training session after 3 months and another obligatory phone call in the 4th week and 8th week after the MPT.

In the case of high-intensity RP, a weekly training session (12 weeks of 90 min each) under therapeutic supervision will be scheduled directly after the MPT. Sixteen weeks and 20 weeks post MPT, obligatory telephone calls with the patient will be conducted. The follow-up training course will be supplemented by another session after 9 months. For patients with a particularly high need for follow-up treatment, a 1-week training course will be offered after 12 months.

The RP offers the advantage of facilitating the patient’s transition into everyday life, accompanying and encouraging progress, as well as enabling early recognition and prevention of relapses. The further development of care thus consists of uninterrupted, seamless and long-term care of patients with back pain following MPT. Another goal is to motivate patients during both the MPT phase and the subsequent 12-month RP phase under multiprofessional guidance to adopt a lifelong active lifestyle. While developing good intentions seems easy, turning them into actions is a challenge. For many, the hurdles to a permanently active lifestyle in everyday life are high.^21^ RP, therefore, serves primarily to provide professional support for the patient in the conscious, voluntary translation of goals and motives into results. For patients suffering from back pain, this can be regarded as a secondary prophylaxis against renewed pain, functional impairment and incapacity to work. In this respect, patients at risk of recurrent back pain are on the same level as patients with other chronic widespread diseases, such as diabetes or cardiovascular diseases, for which there has long been a consensus on appropriate prevention.

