## Aims

The objective of the study is to evaluate the benefit of early and intensive relapse prevention in the context of MPT. The goal is to prevent the chronification of back pain and thus reduce the high direct and indirect costs. To answer this question, outcome, process and cost-effectiveness evaluations will be performed. The aim of outcome evaluation is to examine the intervention effect on patient-relevant outcomes. Process evaluation will examine the extent to which the intervention has been carried out and how the process is perceived and evaluated from the perspective of service providers and patients. Indirect and direct costs will be considered in the health economic evaluation.

From this, the following hypotheses can be derived:

H_1_: the intervention reduces the days of incapacity to work (outcome evaluation).H_2_: the intervention increases the functional capacity (outcome evaluation).H_3_: the intervention is perceived positively by the participating patients (process evaluation).H_4_: the intervention reduces direct and indirect costs (health economic evaluation).

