### Process evaluation

To evaluate the process quality, we will examine the assignment of participants to the standard and the complex programme along with the distribution of the IG to low, medium and high intensity RP. In addition, we will consider usage of the modules (eg, medical training therapy, psychological support and phone consultation) as well as the app utilisation. To examine the quality of the intervention, patients will receive additional questions about their satisfaction with individual MPT and RP modules within the survey. In order to evaluate experiences and satisfaction with the intervention, guided interviews will be conducted. These will be carried out with all physicians, psychologists and physiotherapists involved.

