### Health economic analysis

The health economic analysis will examine the costs, cost savings and cost effectiveness of the intervention. Therefore, intervention costs, expenditures of healthcare utilisation, indirect costs due to incapacity to work and the patient’s health-related quality of life will be assessed. For the calculation of indirect costs, the days of incapacity to work are multiplied by the average hourly wage in Germany, taking into account whether the individuals work full time or part time. The evaluation will be carried out based on claims data. Incremental cost effectiveness will be analysed by considering direct and indirect costs as well as the health-related quality of life of both groups, IG and CG.

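### Indirect costs are built from incapacity days only, so any paid working time spent attending relapse prophylaxis is left out of H4 and the cost-effectiveness result

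*Protocol article*

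**What the plan says.** The section on the health economic analysis names the cost components: "intervention costs, expenditures of healthcare utilisation, indirect costs due to incapacity to work". It then fixes how the last of these is computed: "the days of incapacity to work are multiplied by the average hourly wage in Germany", with allowance for full-time or part-time work. On the source of the data it says: "The evaluation will be carried out based on claims data". The resulting direct and indirect costs feed both H4 (Aims: RP lowers direct and indirect costs, tested two-sided) and the incremental cost-effectiveness analysis.

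The attendance schedule is in the Introduction, in the text after Figure 1. Every path has a 3-hour session on site at 6 months and at 1 year. The medium path adds a session at 3 months. On the high path "a weekly training session (12 weeks of 90 min each) under therapeutic supervision will be scheduled directly after the MPT", with a further session at 9 months. For high-path patients with particularly high need, "a 1-week training course will be offered after 12 months".

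The Abstract says that participants are gainfully employed and that the control group receives nothing further from the trial after the multimodal pain therapy (MPT). Under Process evaluation the article adds that "we will consider usage of the modules".

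**The concern.** The indirect-cost rule recognises one kind of lost work, the incapacity day. An absence of 90 minutes or 3 hours to attend RP is not one. It would hardly show in the claims either: the article's list of limitations notes that certificates usually reach the fund only for incapacity of 3 days or more. MPT attendance is common to both groups and cancels, but RP attendance exists only in the intervention group. The rule therefore credits RP with working time saved and makes no charge for working time that RP may use.

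At stake is the reading of H4 and of the cost-effectiveness ratio. A modest apparent saving in indirect costs could owe part of its size to this accounting rule, and the planned analysis would not show how much.

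**Working it through.** **The plan's own figure.** The expected saving is 40% of 37 days: 0.40 × 37 = 14.8, stated as 15 days (Outcome evaluation; Sample size calculation). This reproduces.

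**Assumptions.** The article does not give these, so I assume:
- an 8 h working day, so 15 days = 120 h;
- 3 h for the 3-month and 9-month sessions, whose length is not stated;
- on the high path, either three follow-up sessions (6, 9 and 12 months) or four (with the 3-month session carried over);
- the 1-year outcome window also applies to costs, with the 1-year session counted inside it;
- travel, telephone calls and the psychological group session (no stated length) left out.

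**On-site hours H per patient, if every hour fell in working time:**

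| Path | Sessions | H | H/8 (days) | H/120 |
|---|---|---|---|---|
| Low | 2 × 3 h | 6 h | 0.75 | 5% |
| Medium | 3 × 3 h | 9 h | 1.1 | 7.5% |
| High | 12 × 1.5 h + 3 or 4 × 3 h | 27–30 h | 3.4–3.75 | 22.5–25% |

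**Average over the intervention group.** The path mix is not given. With equal thirds and the midpoint of 28.5 h for the high path:
- (6 + 9 + 28.5)/3 = 14.5 h
- 14.5/8 = 1.8 days
- 14.5/120 = 12%

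**Sensitivity of that 12%:**
- Mix of 50/30/20 (low/medium/high, with 30 h on high): 0.5 × 6 + 0.3 × 9 + 0.2 × 30 = 11.7 h, about 10%. Mix of 20/30/50: 1.2 + 2.7 + 15 = 18.9 h, about 16%.
- 1-year session placed outside the window (3 h less on each path): (3 + 6 + 25.5)/3 = 11.5 h, about 10%.
- The 15 days read as calendar days: 15 × 5/7 = 10.7 working days, and 1.8/10.7 is about 17%.
- Only a share p of the hours displacing work: p × 12%, so 6% at p = 0.5 and nothing at p = 0.

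**Against sampling error in days.** With the stated SD of 58 and 147 per group, the standard error of the difference is 58 × √(2/147) = 6.8 days before clustering, and 1.8/6.8 = 0.27. The stated effect size implies a smaller SD, 15/0.3409275 = 44, which gives a standard error of 5.1 days and a ratio of 0.35. The article gives no SD for costs, so the same comparison cannot be made for H4 itself.

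**The case against.** Four points weigh against a stronger claim.

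*Working time is not shown.* A reader might infer from the employment criterion that RP sessions take paid hours. No section says so. Sessions could lie outside working hours. The weekly sessions follow directly on MPT in the patients with the most severe complaints, some of whom may still be certified incapacitated, so that their time is already counted. This stands, and it makes every figure above an upper limit under its assumptions.

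*The omission is not purely one-sided.* A reader might infer that only the intervention group's costs are understated. After MPT, patients usually return to a general practitioner or orthopaedist, and time spent on those visits is uncounted in both groups. If RP prevents relapses, the control group would make more such visits, and leaving out their time works against RP. This also stands. As a gauge, if a visit took as long as a weekly RP session (1.5 h), RP would have to avert 14.5/1.5, or about 10, visits per patient to cancel the 14.5 h, with the same share of each in working time.

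*The 1-week course.* Adding it gives much larger shares. At an assumed 12–35 h (4 × 3 h to 5 × 7 h, the weekly hours of standard and complex MPT) the high path reaches 39–65 h, or 32–54% of 120 h. The documents do not support that use. The course is for a subgroup, its hours are not stated, and it comes after 12 months. Its omission may therefore follow from the time horizon, and dividing its hours by a saving within the year mixes two periods.

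*Detail left to the full plan.* Intervention costs are not itemised, and the article refers to a defined analysis plan and to named health-economic standards that are not shown. Cost perspective and sensitivity analyses may well be settled there. The indirect-cost formula, however, is stated in the article, and as stated it does not reach attendance time.

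**Conclusion.** The point holds in a limited form. The stated rule leaves out any paid working time that intervention patients spend at scheduled RP sessions during the year, and so do H4 and the incremental cost-effectiveness result. Where sessions displace work and do not replace usual-care visits, the omission favours RP. The size runs from nothing to about 12% of the planned 15-day saving. The upper end assumes equal thirds on the paths, 3 h for sessions of unstated length, an 8 h day and every hour in working time; the other path mixes and day conventions shown move it between about 10% and 17%. It is small on the low and medium paths and material mainly on the high path.

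A reader might go further and conclude that a cost reduction may be claimed only if it survives charging all RP hours to the intervention group. The documents do not justify that condition. It would turn an unsupported extreme into the decision rule and would itself create an imbalance, because usual-care time would remain uncounted. The matter calls for a sensitivity analysis and leaves the base case as it is.

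**What to change.** Keep the stated indirect-cost rule as the base case and add one prespecified sensitivity analysis to the health economic evaluation:

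- Value the on-site RP hours each intervention patient attended at the same average wage. Take attendance from the module-usage data planned for the process evaluation, after confirming that sessions can be linked to patients and given a duration.
- Report two bounds, with none and with all of these hours counted as working time, excluding time already certified as incapacity.
- Treat outpatient and remedy visits in the claims data the same way in both groups, under a stated assumption on time per visit.
- State whether the H4 and cost-effectiveness conclusions change between the bounds.
- Include the 1-week course only if the cost horizon is extended to cover both its time and its later effects.

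The cost is slightly more analysis, drawn from attendance and claims data that the plan already intends to use, and a cost result that may be slightly less favourable to RP.

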### Multimodal pain therapy

Employees of the AOK Lower Saxony will contact the potentially eligible insured and refer them to the Rehabilitation Center. Before starting MPT, a comprehensive initial examination will be performed by orthopaedists, physiotherapists and psychologists. The MPT programme intensity depends on the severity of the back pain. Patients in the standard MPT group will be treated for 3–4 hours per day, 4 days a week, while patients in the complex MPT will be treated for 5–7 hours per day, 5 days a week. Two groups of eight patients each will be conducted in parallel. The complex therapy group will provide additional treatment and place more emphasis on psychological and medical intervention aspects, while patients in the standard group will be advised to exercise on their own during these times. Overall, it is expected that patients will benefit from the structured approach of the programme.

Modules of the MPT programme will be medical lectures and seminars such as social medicine (eg, payment of wages in the event of illness and professional reintegration), information about the MPT concept and special features of MPT and RP, basic information in different lectures (eg, structure and function of the spine, muscles and health-disease conception: bio-psychosocial model) and seminars addressing common questions on topics such as obesity and back pain or correlations of symptoms with stress, sports, nutrition, medications, surgery, lifting and carrying. Another module will consist of medical consultations once a week, alternating between sessions with and without a physiotherapist or psychologist. In addition, regular medical consultations will take place for support in case of abnormalities in the course of the disease and for individual treatment (manual therapy, medication, etc), if needed. Moreover, psychological-pain therapy lectures and seminars will be carried out by psychologists. These will educate patients about pain and stress, mindfulness, problematic behaviour patterns and setting realistic goals. Psychological training sessions will provide practical implementations in form of relaxation techniques, stress management, progressive muscle relaxation and distraction from pain. In addition to individual psychological consultation, regular psychological counselling sessions will be offered. Finally, physiotherapy, occupational therapy, medical training therapy, sports therapy and a module on motivational and volitional aspects will complete the offer.

